#### Missing Data Considerations

Based on ongoing prospective community mental health studies with comparable follow-up periods [73], we anticipate a clinician dropout rate of approximately 20% over 12 weeks, with minimal patient dropout among retained clinicians since patients are drawn from established caseloads. The mixed effects models described above will provide valid estimates and standard errors under the assumption that dropout is ignorable (ie, dependent only on observed outcomes and participant characteristics). We will conduct additional analyses to assess the sensitivity of our results to this ignorability assumption. Given the study’s sample size, our primary focus will be on overall completion of the 12-week protocol. We will use logistic regression models to examine whether prior outcomes or baseline variables are individually associated with study completion. Variables showing strong associations with completion will be combined into a multiple logistic regression model to predict completion. Based on participant-level dropout probabilities estimated from this model, we will perform exploratory inverse probability–weighted versions of the main mixed effects models and compare intervention effect estimates from the weighted and unweighted models.

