**Methods:**

We will refine the Tele-BE prototype in collaboration with clinicians and supervisors, who are the target end users (aim 1). Working closely with our web development team, we will field test and iteratively refine Tele-BE using rapid-cycle prototyping to optimize user experience and fine-tune the BE strategies (aim 2). The revised platform will then be evaluated in a 12-week open trial involving 30 community mental health clinicians, who will be randomized to either Tele-BE or telehealth as usual. Each clinician will deliver treatment to 2 patients, resulting in a total of 60 patient participants. All sessions will be recorded and coded to assess CBT fidelity. Clinicians and patients will complete questionnaires at weeks 1, 5, 9, and 12, with qualitative interviews conducted at the end of the trial. Primary outcomes will focus on fidelity to CBT structural components, measured via coding of recorded sessions. Secondary outcomes will include target implementation mechanisms—intentions and their determinants (attitudes, norms, and self-efficacy)—assessed using mixed methods, as well as overall CBT fidelity (aim 3). Additionally, trial data will be used to evaluate the acceptability and feasibility of Tele-BE from both patient and clinician perspectives, along with any potential ethical concerns associated with its use (aim 4).

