### Aims 3 and 4: Evaluate the Preliminary Effectiveness of Tele-BE in Engaging Target Mechanisms and Enhancing Clinician Fidelity to CBT

#### Overview

Although aims 3 and 4 are scientifically distinct, study procedures will occur concurrently and are described together. We will randomize 30 clinicians who already provide individual CBT via telehealth for at least 2 clients to either Tele-BE or telehealth as usual (Tele-AU), with 15 clinicians per condition. Allocation will be balanced within organizations to ensure equal representation across conditions within each agency. Each participating clinician will deliver treatment to 2 patients over 12 weeks, the standard length for many CBT protocols, and clinician fidelity to CBT structural components will be tracked in each condition. While the primary goal is to evaluate the feasibility of our design and measurement approach for a fully powered trial, we will also measure patient symptoms, therapeutic alliance, and patient-centered care to explore preliminary clinical effectiveness outcomes and assess any potential concerns with Tele-BE (eg, clinician distraction or impact on therapeutic alliance) using mixed methods.

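### The check on ignorable dropout relies on completion models and weights that need an ignorability assumption of the same kind, fitted to about 6 clinician dropouts

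*Protocol article*

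**What the plan says.** All of this is in Missing Data Considerations unless stated otherwise.

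- **The assumption.** The mixed models are said to be valid "under the assumption that dropout is ignorable (ie, dependent only on observed outcomes and participant characteristics").
- **The promise.** "We will conduct additional analyses to assess the sensitivity of our results to this ignorability assumption."
- **The method.** "We will use logistic regression models to examine whether prior outcomes or baseline variables are individually associated with study completion." Then: "Variables showing strong associations with completion will be combined into a multiple logistic regression model to predict completion." The resulting dropout probabilities feed weighted versions of the main mixed models, which the article calls exploratory. The intervention effect is compared with and without weights.
- **The expected amount.** "we anticipate a clinician dropout rate of approximately 20% over 12 weeks". For the patients of clinicians who stay, the article expects losses to be small: "with minimal patient dropout among retained clinicians since patients are drawn from established caseloads".
- **The sample.** Clinicians are randomized "to either Tele-BE or telehealth as usual (Tele-AU), with 15 clinicians per condition" (Overview of aims 3 and 4). "Each clinician will deliver treatment to 2 patients, resulting in a total of 60 patient participants" (abstract, Methods).

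No analysis that departs from ignorability is named.

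**The concern.** The article defines ignorable dropout as dropout that depends on observed data alone. It then offers to test that assumption with methods that see observed data alone. A statistical analysis plan that follows this section would inherit the mismatch, and the report could claim robustness to an assumption that was never relaxed.

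Non-ignorable dropout is plausible here, though not established. The protocol itself anticipates that Tele-BE might distract clinicians (Overview), intrude on their autonomy (Aim 1) or put pressure on them (Aim 4 primary outcomes; Ethical Considerations). Fidelity is scored from recorded sessions, so it is unseen once a clinician leaves. If clinicians leave Tele-BE because their fidelity is about to fall, the between-arm fidelity trend used under Progression Criteria would look too favourable.

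The second worry is the amount of data behind the weights, because the number of clinician dropouts will be small.

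**Working it through.** The article prints no event count or precision for the completion models, so there is no stated figure to reproduce. Its related counts agree: 30 × 2 = 60 patients, and 60 × 12 = 720 sessions.

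**1. What each method assumes.** Let H be a clinician's observed history and Y the later fidelity that goes unseen after dropout. Define δ = E(Y | H, retained) − E(Y | H, dropped out).
- The mixed model predicts Y for dropouts from the observed outcomes and its covariates. This sets δ = 0 given those variables.
- Weighting lets retained clinicians with similar H stand in for dropouts. This sets δ = 0 given the variables in the completion model.

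Both estimates are functions of the observed data. Two situations with the same observed data but different δ give the same weighted estimate, the same unweighted estimate and the same gap between them. The gap therefore carries no information about a δ that remains after conditioning on everything measured.

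**2. Illustration by simulation (assumed parameters).** The true effect was 0, with one earlier and one later outcome correlated 0.6. Results are in units of the simulated outcome.

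| Scenario | Unweighted | Weighted |
|---|---|---|
| Large sample, dropout driven by the observed earlier outcome | −0.001 | −0.002 |
| Large sample, dropout in one arm driven by the unseen later outcome, 15% lost | 0.169 | 0.169 |
| 30 clinicians, same unseen mechanism | 0.178 | 0.177 |

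In the last two rows the estimates agree and both are biased.

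**3. What the comparison can show (assumed parameters).** The true effect was 0, about 21% of Tele-BE dropped out because of a measured burden score, and burden also lowered later fidelity. The unweighted bias was 0.088. It was 0.051 with burden in the weights and 0.000 with burden by arm. Here the two estimates diverge, so the comparison does give a warning.

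**4. Events behind the weights.** Expected clinician dropouts = 0.20 × 30 = 6, or about 3 per arm, with a binomial 95% range of 2 to 11. At 10% to 30% dropout, 3 to 9 are expected. The 6 × 2 = 12 patients lost with them are the same 6 clinician events.

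Table 2 alone offers 10 clinician-level candidate predictors: fidelity, intentions, attitudes, norms, self-efficacy, acceptability, feasibility, usability, supervision practices and social desirability.
- *Power to detect one binary predictor* (15 v 15, average dropout 20%, two-sided 5%): 11% for an odds ratio of 2, 20% for 3, 28% for 4 and 35% for 5.
- *Model failure.* In the 30-clinician simulations a two-predictor completion model failed or separated in 10% of runs (observed mechanism, 5.6 events on average) and 19% (unseen mechanism, 4.5 events on average). With 6 events and every predictor differing by 0.7 SD, separation was 3%, 8% and 26% for 3, 4 and 5 predictors. A repeat of that second setting gave 3%, 11% and 25%, and under 1% for two predictors.

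The rates depend on the scenario.

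**5. Size of the bias.** The bias in the 12-week mean difference = Tele-BE dropout fraction × share of weeks missing × δ, with δ = 0 in Tele-AU. The share missing (0.5) and δ are assumptions.
- 20% dropout, δ = 1 component: 0.2 × 0.5 × 1 = 0.10
- 40% dropout, δ = 1: 0.4 × 0.5 × 1 = 0.20
- 40% dropout, δ = 1.5: 0.4 × 0.5 × 1.5 = 0.30

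Note that 40% of 15 is 6 clinicians, which puts every anticipated dropout in one arm.

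**The case against.** The strongest reply is that weighting does condition on more than the mixed model does. The covariates named under Quantitative Analyses are patient demographics. The completion model may use any earlier outcome or baseline variable. The obvious route to dropout, burden from the prompts, is partly measured before it happens: acceptability, feasibility and usability at weeks 1, 5 and 9, intentions and attitudes, and overrides in the web analytics. This stands. A reader might infer that the check would report robustness whatever the truth, and the documents do not support that. Step 3 shows it can raise an alarm. It is blind only to dropout that no variable in the completion model explains.

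Three further points also stand:
- The article calls the weighting exploratory and refers to the sample size. It fixes no number of predictors, so the higher separation rates need a model larger than it specifies.
- A reader might take 0.10 to 0.30 components as an estimate of bias. The protocol gives no value for the shift or the timing of dropout, so these are illustrations.
- A reader might infer from the phrase participant-level that both patients of a departing clinician would be entered as independent dropouts. Clinicians are participants too, and the section states dropout at clinician level. This is a reading to rule out, not a stated plan.

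One argument does not stand: that this belongs to the statistical analysis plan, which is not shown. The lack of a delta analysis would not be a finding on its own. The finding is that the article itself gives the weighting a purpose it cannot serve.

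**Conclusion.** The concern holds in a limited form. The named analyses remain within the ignorable framework, so agreement between weighted and unweighted results must not be reported as robustness to non-ignorable dropout. They keep some value as a check on measured variables missing from the mixed model. This conclusion follows from the section's own definition and needs no assumed number.

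The instability rests on the article's 20% dropout in 30 clinicians, about 6 events. The exact failure rates are assumption-dependent.

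The possible bias is about 0.10 of a component at the anticipated 20% dropout, if unseen fidelity is 1 component lower and half the weeks are lost. It reaches 0.30 only under the extreme inputs shown.

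Severity is moderate. This is an exploratory analysis in a pilot whose stated main goal is feasibility and whose progression rule looks at trends, without a significance test or margin.

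**What to change.** 1. **Rename and restrict the weighting.** Describe it as an exploratory check within the ignorable (missing at random) framework. Fit the completion model at clinician level with very few predictors named in advance, using penalised (Firth) estimation if needed, in place of one-at-a-time screening.
2. **Add a clinician-level delta-adjusted analysis as the sensitivity analysis.** Impute post-dropout sessions under the mixed model. Lower them by a stated range, for example 0.5, 1.0 and 1.5 components (assumed values), in Tele-BE alone and then in both arms.
3. **Report it in terms that fit the progression rule.** Show how the between-arm fidelity estimate and its interval move, and the shift at which a trend favouring Tele-BE disappears. No significance threshold is needed.

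Cost: a paragraph of text and a little extra programming. No new data, visits or participants.

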#### Qualitative and Mixed Methods Analyses

All interviews will be audio-recorded and transcribed for thematic analysis to complement quantitative data, allowing examination of target mechanism engagement (aim 3), Tele-BE acceptability and feasibility, and potential ethical concerns (aim 4). Given our interest in understanding clinician and patient experiences separately, interviews from these groups will be analyzed independently. Qualitative coding for both clinician and patient interviews will proceed in 6 stages. First, the coding team will familiarize themselves with the data by reading all transcripts and noting initial reactions. Team members will then debrief and share observations after reviewing all transcripts. Second, the coding team will develop an initial set of codes through line-by-line open coding of 2 randomly selected transcripts. Each team member will code the transcripts independently, then reconvene to compare codes and reach consensus. This consensus coding process enhances trustworthiness in data analysis and helps account for individual values and biases that may influence coding [74]. While reviewing the transcripts, the team will create a codebook documenting code descriptions to facilitate organization and reflection. The codebook will likely be guided by a combination of a priori areas of interest (eg, Tele-BE’s impact on motivation to use structural components, acceptability of Tele-BE, and its effect on reducing cognitive burden in CBT delivery) as well as emergent themes arising directly from the data. Following codebook creation, the coding team will independently code all remaining transcripts line-by-line, compare codes, and reach consensus on coding decisions. The codebook will be iteratively updated as new codes emerge, capturing additional clinician and patient experiences revealed in the interviews. Third, the team will cluster codes based on shared patterns in content and generate themes that describe these patterns. Fourth, themes will be compared against quotes from the coded data to ensure they accurately reflect participant experiences. The team will refine themes by consolidating similar themes and breaking broader themes into subthemes as needed. Fifth, the team will finalize names and descriptions for all themes and subthemes. Finally, findings will be presented using illustrative examples from the coded data. To further enhance trustworthiness, coding team members will maintain analytic memos documenting their thought processes regarding codes, subthemes, and themes, supporting reflection on how values and biases—particularly related to Tele-BE—may have influenced coding decisions.

We will then conduct mixed methods analyses following best-practice recommendations to contextualize and interpret our quantitative findings [75-77]. Specifically, we will compare qualitative themes among therapists with low, medium, and high fidelity in Tele-BE, focusing on instances of overriding Tele-BE nudges, perceived ease of use, and any ethical concerns. Additionally, we will examine how patient ratings of therapeutic alliance are informed by their qualitative experiences with therapists using Tele-BE, and explore differences in patient-reported themes among therapists with varying levels of fidelity to structural CBT components.

#### Progression Criteria

We will examine acceptability and feasibility data, as well as trends in observed fidelity, to determine whether the pilot trial results support progression to a larger, confirmatory trial. For acceptability and feasibility, we will descriptively compare mean AIM and FIM scores between Tele-BE and Tele-AU clinicians; comparable scores would support the utility of progressing. If Tele-BE scores are notably lower than those in the Tele-AU condition, this would raise concerns regarding its acceptability and feasibility. Regarding fidelity, we will look for trends indicating (1) greater use of structural components in the Tele-BE condition relative to Tele-AU as measured by the CTRS, or (2) increased motivation to use CBT structural components in Tele-BE relative to Tele-AU, as suggested by qualitative analysis.

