##### Participants and Procedures

We will identify at least 4 local agencies that use telehealth and have participated in system-sponsored BCI CBT training [55] as recruitment sites. A cascaded recruitment strategy, previously successful in other studies, will be employed to recruit 30 CBT-trained clinicians who treat study-eligible patients (ie, age 14 or older, consistent with the local age of consent for mental health services; already deemed appropriate for CBT; and already using telehealth as their preferred therapy modality). In this approach, clinicians will then help select 2 patients with whom they plan to use CBT and will approach those patients about participating in the study. If a clinician has more than 2 patients with whom they plan to use CBT, 2 patients will be randomly selected from the larger pool for study participation. After obtaining informed consent, clinicians will be randomized to either the Tele-BE or Tele-AU condition. Study procedures will be identical across conditions, with the only difference being that clinicians in the Tele-BE condition will use the new telehealth tool, while those in the Tele-AU condition will use the telehealth methods established by their organization. All sessions will be video-recorded using encrypted, HIPAA-compliant technology via the clinicians’ assigned telehealth platform. Clinicians and patients will complete questionnaires at 4 time points—baseline/week 1, week 5, week 9, and week 12—and participate in a qualitative interview posttrial (Table 2).

Clinicians will receive US $150 for completing study measures (US $50 for week 1 and posttrial, US $25 for weeks 5 and 9). Patients will receive US $5 per session for providing brief self-report data and allowing their sessions to be recorded, for a maximum of US $60; those completing qualitative interviews will receive an additional US $25. Clinicians and patients in both conditions will follow the same study activity schedule and complete the same assessment battery, except that participants in the Tele-BE condition will also respond to condition-specific qualitative interview questions. Compensation rates are consistent with our prior work.

**Table 2 table2:** Trial assessment schedule for aims 3 and 4.

Outcomes		Measures	Tele-BE^a^																										Post
				1		2		3		4		5		6		7		8		9		10		11		12			

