**Aim 4 primary outcomes**																													
	Acceptability	AIM^d^ [58] and Interview	✓		N/A		N/A		N/A		✓		N/A		N/A		N/A		✓		N/A		N/A		N/A		✓		
	Feasibility	FIM^e^ [58] and web analytics	✓		N/A		N/A		N/A		✓		N/A		N/A		N/A		✓		N/A		N/A		N/A		✓		
	Usability	SUS^f^	✓		N/A		N/A		N/A		✓		N/A		N/A		N/A		✓		N/A		N/A		N/A		✓		

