#### Quantitative Measures: Aim 4 Primary Outcomes

Primary outcomes for aim 4 include Tele-BE acceptability, feasibility, and any potential ethical concerns raised by clinicians or patients regarding the platform. Acceptability will be assessed using the AIM [52]. Feasibility will be examined through a combination of the FIM [52] and web analytics data. Tele-BE usability will be evaluated using the SUS [53]. Psychometric support for these measures has been described above under aim 1 activities. All measures will be administered to clinicians in both conditions to allow comparison of quantitative scores for acceptability and feasibility. These measures will be supplemented with clinician and patient interviews, which will also assess potential ethical concerns, including any pressure clinicians may have felt from the platform to deviate from care they believed was in the best interest of their patients.

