#### Qualitative: Clinician Interviews (Aims 3 and 4)

All clinicians, regardless of condition, will complete interviews after their patients finish the trial period. The first portion of the interview will be identical for all clinicians and will explore perceptions of their intentions and the determinants of intentions to use CBT structural components throughout the trial. This portion addresses aim 3 questions regarding engagement of target mechanisms. Questions will be adapted from an established theory-guided qualitative interview [72], which includes items on attitudes toward an EBP, self-efficacy, perceived norms, and motivation. Questions will be asked separately for each structural CBT component of interest (Table 1). All clinicians will also be asked about barriers they encountered during the trial in using structural components, with specific probes regarding the impact of cognitive burden on delivery (eg, “To what extent, if at all, did factors like forgetting due to competing demands make it easier or harder for you to set an agenda?”). Collecting these responses from all clinicians will allow us to examine themes by condition to determine whether Tele-BE better engaged target mechanisms and reduced barriers to structural component delivery. The second portion of the interview will be administered only to clinicians randomized to Tele-BE and will address aim 4 by querying acceptability and any feasibility issues that arose. Patient interview questions may include, “How was your experience with Tele-BE? What aspects were easy or difficult to use?” We will also use self-reported fidelity data collected via web analytics to ask clinicians specific questions about how they decided to act on or override Tele-BE nudges (eg, electing not to review a planned homework) and their rationale for doing so. Clinicians will also be asked about any ethical concerns they or their patients might have, such as undue pressure to deliver structural CBT components or potential negative impacts on treatment processes. Finally, clinicians will be queried about any unanticipated resources required to engage with Tele-BE and asked to estimate how the platform influenced the time needed to prepare for or document a therapy session, informing our cost estimates.

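### The acceptability and feasibility progression rule rests on parity with Tele-AU and sets no minimum for Tele-BE itself, so comparable AIM and FIM means say little about whether Tele-BE is acceptable

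*Protocol article*

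**What the plan says.** The Progression Criteria section gives one favourable and one unfavourable reading of the AIM and FIM data. The favourable one is set out as: "we will descriptively compare mean AIM and FIM scores between Tele-BE and Tele-AU clinicians; comparable scores would support the utility of progressing". The unfavourable one is: "If Tele-BE scores are notably lower than those in the Tele-AU condition, this would raise concerns regarding its acceptability and feasibility". Neither comparable nor notably lower is given a number, and no score is named that Tele-BE must reach in its own right.

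The aim 4 primary outcomes section defines the target as the acceptability and feasibility of Tele-BE, together with any ethical concerns about it. It measures acceptability by AIM, feasibility by FIM plus web analytics, and usability by SUS, supplemented by interviews. It adds: "All measures will be administered to clinicians in both conditions to allow comparison of quantitative scores for acceptability and feasibility". Participants and Procedures says that "those in the Tele-AU condition will use the telehealth methods established by their organization". The Overview of aims 3 and 4 says that all 30 clinicians already provide CBT by telehealth and that 15 go to each arm.

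Table 2 schedules AIM, FIM and SUS at weeks 1, 5 and 9 and post-trial. On attrition, Missing Data Considerations states: "we anticipate a clinician dropout rate of approximately 20% over 12 weeks".

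**The concern.** The aim 4 question is whether clinicians find Tele-BE acceptable and workable. The progression rule asks something else: whether Tele-BE clinicians score about as high as clinicians who never used it. The reference is then whatever Tele-AU clinicians think of their usual arrangements, or possibly of a tool they have not seen. Parity with that reference can arise because both are liked, because both are disliked, or because the sample is too small to show a gap. Only the first is a reason to move to a confirmatory trial, and the rule does not separate the three. This comparison is the stated quantitative basis for the acceptability and feasibility part of the progression decision.

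**Working it through.** **What each arm rates.** Tele-BE clinicians have used the new platform, and Tele-AU clinicians have used their organization's existing one. The aim 1 section describes AIM and FIM as scales about an innovation, and Tele-AU clinicians receive none. The article does not give the item wording for Tele-AU. The likeliest object is their incumbent platform; the alternative is a tool they have not used. On either reading the two means are not ratings of the same thing after the same experience.

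**What parity allows.** The rule is a statement about a difference between means. Any common level satisfies it, including a low one, because no floor is given.

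**How precise the difference is.** The plan states no SD, margin, alpha or power for this rule, so there is no figure to reproduce. The results are therefore in SD units and assume equal SDs in the arms. Inputs: 15 clinicians per arm (Overview of aims 3 and 4); about 20% dropout (Missing Data Considerations), so 15 × 0.8 = 12 per arm if losses are equal.

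Half-width of the 95% interval for the arm difference = t(0.975, 2n − 2) × √(2/n):
- n = 15: 2.048 × 0.365 = 0.75 SD
- n = 12: 2.074 × 0.408 = 0.85 SD

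**How often a real deficit would look comparable.** Assume that notably lower means an observed gap of at least 0.5 SD. The normal approximation has standard error √(2/n), which is 0.365 SD or 0.408 SD.

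| True Tele-BE deficit | Arms look comparable, n = 15 | n = 12 |
|---|---|---|
| 0.3 SD | 71% | 69% |
| 0.5 SD | 50% | 50% |
| 0.8 SD | 21% | 23% |

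With no true difference, concern would be raised 8.5% (n = 15) to 11% (n = 12) of the time.

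For scale, formal non-inferiority to Tele-AU (one-sided 0.025, 80% power) would need about 175, 63 or 25 clinicians per arm for assumed margins of 0.3, 0.5 or 0.8 SD. A pilot need not do this. The figures show only that parity at 12 to 15 per arm carries little information.

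**The Tele-BE mean on its own.** Half-width = t(0.975, n − 1)/√n:
- n = 15: 2.145/3.873 = 0.55 SD
- n = 12: 2.201/3.464 = 0.64 SD

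This is still wide, but narrower than for the difference, and it bears directly on Tele-BE.

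**Dropout and a single-arm mean.** If 20% leave and would have scored g SD below those who stay, the stayers' mean exceeds the full-arm mean by 0.2 × g. That is 0.1, 0.2 or 0.4 SD for assumed g of 0.5, 1 or 2.

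**The case against.** The comparison is labelled descriptive, and comparable scores are said only to support progressing, not to prove acceptability. Whether nudges cost acceptability relative to usual telehealth is a fair question. The section opens by referring to acceptability and feasibility data generally, and overrides, interviews and web analytics are all collected. AIM, FIM and SUS are also taken on Tele-BE alone in aim 1, and aim 2 continues until a version fit for formal testing is reached. All of this stands, and it lowers the chance that a poorly accepted tool enters the trial. It does not supply a level that Tele-BE must reach in aim 3, and the sentence that applies the rule names only AIM and FIM.

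Two stronger readings are tempting, and the documents do not support them. A reader might infer that a well-liked Tele-BE scoring slightly below Tele-AU fails the rule; the text reserves concern for notably lower scores. A reader might also infer that the rule covers completers only and is therefore biased upward. No such restriction is stated, and clinicians who leave may already have given ratings at weeks 1, 5 or 9. Bias in the arm difference would also require dropout, or the gap between leavers and stayers, to differ by arm. The interview section says "All clinicians, regardless of condition, will complete interviews after their patients finish the trial period"; it does not say that those who withdraw are excluded.

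It is also fair to say that the single-arm alternative is imprecise, is itself exposed to loss of dissatisfied clinicians, and needs a benchmark that these documents do not contain. The fix has to deal with each of these.

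**Conclusion.** The point holds as a weakness in a rule the plan does state. Parity with Tele-AU, without a floor for Tele-BE, does not answer the aim 4 question and would be met by two equally poor means. The evidence it gives against a deficit is also thin, with a half-width of 0.75 to 0.85 SD on the difference. These widths assume equal SDs and, for the larger one, 20% dropout in each arm. The probabilities in the table further assume a 0.5 SD cut-off for notably lower. That the two arms rate different objects is a strong inference from what each arm uses; the item wording would settle it. It is not shown that the rule as written is biased or limited to clinicians who stay.

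**What to change.** Rewrite the acceptability and feasibility part of the Progression Criteria:

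- Make the criterion the Tele-BE clinicians' own mean AIM, FIM and SUS at the post-trial assessment, reported with confidence intervals, against benchmarks that the sponsor fixes and justifies before aim 3 enrolment.
- Add Tele-BE use from web analytics, which the plan already treats as part of feasibility, with its own pre-set benchmark.
- Keep the Tele-AU scores as descriptive context, and state what Tele-AU clinicians are asked to rate.
- Offer AIM, FIM, SUS and the ethics questions to any clinician who withdraws. Report the Tele-BE mean with and without leavers' last available ratings, noting that those ratings reflect shorter exposure.

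The instruments and web analytics are already in the plan. The cost is one revised paragraph, exit contacts with about 6 clinicians (20% of 30, across both arms), and the sponsor's commitment to absolute benchmarks, which must be justified from outside these documents.
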